## Abstract

**Background:**

Upper limb spasticity (ULS) is a common complication after stroke, which seriously affects the quality of life and rehabilitation of patients. There are different treatment methods for post-stroke spasticity (PSS). Our group found that functional acupuncture (FA) can effectively improve forearm spasticity and hand dysfunction after stroke, but the efficacy of ULS needs to be further verified. Therefore, this subject has mainly used clinical randomized controlled trials to evaluate the clinical efficacy of FA in the treatment of ULS after ischemic stroke.

**Method:**

This is a parallel design and randomized controlled trial. We selected 108 patients who met the predefined criteria and randomized them into two groups, the experimental group and the control group. The experimental group receives FA and routine rehabilitation treatment. The control group received traditional acupuncture (TA) and routine rehabilitation treatment. All patients received 20 courses of treatment for 4 weeks, and the modified Ashworth score (MAS), clinical neurological deficit score (CSS), Fugl-Meyer upper extremity function assessment (FMA-UE), and the Modified Barthel Index (MBI) scores were evaluated before and after treatment.

**Discussion:**

This trial is mainly to study the clinical efficacy of FA in the treatment of ULS after ischemic stroke. It will not only provide a new idea for the clinical treatment of upper limb post-stroke spasticity (ULPSS) but also will provide effective experimental support and a theoretical basis for the clinic.

**Trial registration:**

China Clinical Trials Registry No. ChiCTR2100050440. Registered on 27 August 27 2021.

## Introduction

Stroke is an acute or focal brain dysfunction caused by various vascular causes, such as hemorrhage and ischemia, with high incidence rate, disability rate, and mortality rate (1, 2). Ischemic stroke is the most common form, with 87% of all strokes (3). Limb spasticity is one of the common complications of a stroke, which seriously affects the functional recovery of patients, especially in the upper limbs (4). There is no clear definition of spasticity but is often defined as a motor disorder characterized by a velocity-dependent increase in tonic stretch reflexes after upper motor neuron syndrome (5, 6). The upper limb projection area accounts for a large proportion in the cerebral cortex, there can be more obvious functional damage to the upper limb after the lesion, so the upper limb spasticity (ULS) is more serious than that of the lower limb (7). The ULS may cause problems related to (1) passive function (e.g., wearing, eating, and cleaning hands); (2) pain; and (3) muscle and joint contractures (8). It can directly affect the quality of daily life of patients, the difficulty of recovery is significantly higher than that of lower limbs, and it can bring heavy pressure and economic burden to the patient's family and society (9–11). Therefore, it has a wide range of clinical significance to find an effective treatment for upper limb post-stroke spasticity (ULPSS).

In recent years, more and more attention has been paid to the issue of spasticity. At present, western medicine has no specific and systematic treatment method for ULPSS. It mainly conducts rehabilitation training, such as physical therapy, drug therapy, botulinum toxin A (BoNT-A), and external mechanical adjuvant therapy (12–14). However, each traditional treatment method has its limitations. There is no fixed standard for the parameters and stimulation intensity of physical therapy, which only depends on personal preference and experience (15). Although drug therapy has obvious effects, it is prone to side effects, such as sleepiness, fatigue, nausea, and muscle weakness (16). Long-term injection of BoNT-A may cause local pain, muscle weakness, edema at the injection site, and other adverse reactions and cannot significantly improve the quality of life and limb function of patients with post-stroke spasticity (PSS) (17). Traditional Chinese Medicine (TCM) treatment focuses on acupuncture and moxibustion, massage, Chinese medicine rehabilitation nursing, hot compress, and external application of Chinese medicine, which has a good curative effect and is widely used (18–20). At present, many studies have shown that TCM is very effective in the treatment of stroke hemiplegia with acupuncture. Stimulating acupoints through acupuncture can stimulate brain cells to activate after stimulation and promote the establishment of cerebrovascular collateral circulation in patients. It has been widely used in the treatment of PSS (21, 22). In addition, the results of clinical trials and meta-analysis show that acupuncture can significantly improve the grade of spasticity, help patients to restore muscle tension and motor function, improve the quality of life, and reduce the disability rate (23). Because of its unique advantages, such as significant curative effect, low price, and small side effects, it is favored by more and more clinicians and patients and results in a lot of innovative acupuncture methods.

Our group through reviewing the literature and combining with a summary of clinical practice experience found that the use of functional acupuncture (FA) can effectively improve forearm spasticity and hand dysfunction after stroke (24–26), but the efficacy of ULS needs to be further verified. FA is a new acupuncture method that combines traditional acupuncture (TA) with modern rehabilitation theory and selects two common acupoints and two functional points to maximize the recovery of patients' various functions (27). FA can enhance sensory transmission, simplify acupoints, and have a great effect. It can be divided into three steps: rapid needling of the acupoint Daling (PC7), penetrating needling of the acupoint Hegu (LI4), and electrical stimulation of the functional acupoint. After rapid needling at PC7, the contracture fingers can be relaxed to a state of no flexion, passive activity, and no resistance and can last for several hours (28). The penetrating needling of LI4 to Houxi (SI3) can directly alleviate the spasticity of finger flexor muscle and indirectly excite and stretch the extensor tendon of a finger. By repeatedly stimulating the flexor tendon, the spasticity can be alleviated and the effect of improving finger dysfunction can be achieved (18, 29). In this state, the use of functional acupoint electrical stimulation can quickly improve the overall function of the upper limb. Then this topic is mainly to study the clinical efficacy of FA in the treatment of ULS after ischemic stroke.

In recent years, clinical experiments and basic research have found that acupuncture has an obvious therapeutic effect on ULPSS, it is considered by the World Health Organization (WHO) as an alternative and complementary strategy for the treatment and improvement of stroke (23), but the efficacy differences between different acupuncture methods are uncertain. Few trials involve the comparison of different acupuncture methods to verify the efficacy differences between different acupuncture interventions. In this study, FA was used to treat ULS after ischemic stroke, verifying the efficacy and rehabilitation significance of FA, which makes up for the study on the lack of different acupuncture methods in this disease, enriching the treatment of the ULSPSS, and providing a reference for clinical treatment of this disease.

## Methods and Analysis

### Trial Design and Setting

This was a parallel design and randomized controlled trial. The subjects were be recruited from the Rehabilitation Center of the First Affiliated Hospital of Henan University of Chinese medicine. We selected 108 patients who met the predefined criteria and randomly divided them into 2 groups, with 54 patients in each group: the experimental group and the control group. All patients received 20 courses of treatment for 4 weeks, and the upper limb function was evaluated before and after treatment. The efficacy of the experimental group when compared with the control group was analyzed after data collection. An example template for the content of admission plans, interventions, and evaluations is shown in Table 1. Our protocol presentation is in accordance with the Standard Protocol Items: Recommendations for Interventional Trials 2013 (SPIRIT 2013) guidelines (30). The study flowchart is presented in Figure 1.

**Table 1 T1:** Qualification screening and informed consent was completed before the assignment.

**Timepoint**	**Enrollment**	**Allocation**	**Treatment period**			
	**−1 week**	**0 week**	**1 week**	**2 week**	**3 week**	**4 week**
Enrollment						
Eligibility screen	X					
Baseline	X					
Informed consent	X					
Medical history	X					
Merger disease	X					
Allocation		X				
Interventions						
Experiment group			X	X	X	X
Control group			X	X	X	X
Assessments						
MAS		X				X
FMA-UE		X				X
CSS		X				X
MBI		X				X
Safety evaluation		X				X
Needle sensation			X	X	X	X
Adverse events			X	X	X	X

*After allocation, each patient was treated within 4 weeks. The clinical outcome was evaluated twice: after allocation and after treatment. Adverse events were recorded on the case report form (CRF) at any time during treatment*.

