### Randomization

Eligible patients were allocated, in a 1:1 ratio were randomly assigned to the experimental group or the control group, following the randomization principle, which employs block randomization to generate random-number sequence using the SPSS, and an independent statistician who did not participate in the treatment and result evaluation was responsible for processing the results. Meanwhile, we also prepared sealed opaque envelopes with group information strips in these envelopes, which was hidden until the informed consent was obtained.

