### Blinding

Due to the limitations of this protocol and the nature of acupuncture treatment, the acupuncturists participating in this trial could not be blinded to the assignments, the patients were blinded. Patients were informed that they will be randomized to receive one of two effective interventions after registration. Every patient knew the type of treatment they received, but they did not know another type. Each patient's acupuncture intervention was carried out in a separate personal space and at different times to avoid communication between patients. The distribution of patient groups by data managers and statisticians was not clear. Experts, data managers, and statisticians were not allowed to communicate with others about patients' treatment, so as to improve the accuracy of test indicators and ensure the effectiveness of interventions and the objectivity and reliability of the evaluation. The blind method was made public after the statistical analysis was completed.

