### Inclusion and Exclusion Criteria

Inclusion Criteria. The Eligible Participants Should Meet all of the Following Criteria:

(1) The patients met the diagnostic criteria of ischemic stroke and were diagnosed by computed tomography (CT) or magnetic resonance imaging (MRI).

(2) Patients with clinical symptoms of paralysis on one side of the limb and upper extremity motor dysfunction.

(3) Patients with the MAS is the grade I and above, grade III and below.

(4) Men or women with an age range between 20 and 70 years.

(5) The Brunnstrom recovery stage (BRS) of the patient's upper extremity ranged from II to IV.

(6) Patients who are stable, conscious, and have no communication problems.

(7) Patients with no previous history of upper extremity dysfunction, first onset, or legacy of stroke.

(8) The participants were voluntary and signed the relevant informed consent.

Exclusion Criteria. Criteria for Exclusion Are the Following:

(1) Patients with upper extremity motor dysfunction, combined with severe cardiovascular disease, hypertension, respiratory infection, severe renal dysfunction, severe diabetes mellitus, and a history of psychiatric, were accompanied by agnosia, apraxia, and an intellectual disability that affects communication and evaluation.

(2) Patients with unstable vital signs in the acute phase.

(3) Patients in thrombolytic therapy.

(4) Fear of acupuncture and poor physical fitness, such as easy to faint, are not suitable for acupuncture treatment of patients.

(5) Patients who have taken sedative drugs and muscle relaxants in the recent past.

(6) Patients with transient ischemic attack (TIA), reversible ischemic neurological deficits, subarachnoid hemorrhage, etc.

(7) Patients who are pregnant, lactating, or preparing for pregnancy.

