### Recruitment

We had formulated plans and methods related to subjects, such as preparing informed consent, and obtaining necessary data, videos, and pictures to help subjects to understand the purpose and procedure of the trial. We had also explained the advantages and disadvantages of this treatment and relevant safety measures to be taken during the trial.

In addition, we had put up recruitment posters in hospitals and community billboards and used the Internet for publicity and recruitment. The research group had conducted preliminary judgment and screening on each participant according to the above inclusion and exclusion criteria, conducted a final review after signing the informed consent, and those who passed the review were included in the test.

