#### Primary Outcomes

The main result is the MAS, which is the most widely used clinical spasm scale (32). It is usually used to obtain the baseline evaluation of increased muscle tone, monitor the course of the disease, determine the effectiveness of drugs, and rehabilitation interventions, so as to reduce the overall increase of muscle tension, normalize the muscle tone of the selected muscle group, and guide physical therapy and other treatment decisions. It has the advantages of simplicity, time saving, and convenient operation. It is divided into 6 levels, i.e., 0, I, I +, II, III, and IV. Scoring methods, i.e., 0, 1, 2, 3, 4, and 5 points, represent 0, I, I +, II, III, and IV, respectively. The higher the MAS score, the more serious the spasticity. Compared with the lower limbs, the reliability of the upper limbs is better (33). The specific contents of MAS are shown in Table 3.

**Table 3 T3:** The modified Ashworth score (MAS)-specific scoring rules.

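### Baseline MAS and the three secondary scales are scheduled after allocation with no stated rater blinding, and the stated end of concealment needs reconciling with the later eligibility review

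*Protocol article*

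**What the plan says.** **Timing of the baseline scales.** The note under Table 1 (Trial Design and Setting) reads: "The clinical outcome was evaluated twice: after allocation and after treatment". In the grid, MAS, FMA-UE, CSS and MBI each have two ticks, one in the week 0 column headed Allocation and one at week 4. A row called Baseline is ticked at week -1, but its content is not given and none of the four scales is ticked there.

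**Role of the MAS.** It is the primary outcome: "The main result is the MAS, which is the most widely used clinical spasm scale". It is also an entry criterion: "Patients with the MAS is the grade I and above, grade III and below".

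**Who knows the arm.** The Blinding section says that "the acupuncturists participating in this trial could not be blinded to the assignments, the patients were blinded". It describes data managers and statisticians as unaware of the groups, and it bars them and certain experts from discussing patients' treatment. Outcome Assessments says that the data collectors are trained. Neither section says that the people who rate the MAS are blinded.

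**Concealment and eligibility.** Randomization describes sealed opaque envelopes holding the group assignment, "which was hidden until the informed consent was obtained". Recruitment says that the research group "conducted a final review after signing the informed consent, and those who passed the review were included in the test". On the other side, the title of Table 1 reads "Qualification screening and informed consent was completed before the assignment", and Randomization opens with "Eligible patients were allocated, in a 1:1 ratio were randomly assigned to the experimental group or the control group".

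**The concern.** A baseline value protects a comparison only if it cannot depend on the arm. The simplest guarantee is to record it before anyone can know the assignment. Here the article places it afterwards, for a scale graded by an examiner's judgement of resistance to passive movement. If the rater knows or guesses the arm, the grade can shift without any intent to mislead. Expressly stated rater blinding would be the other protection, and the article does not give it.

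The eligibility wording raises a related but weaker question. Concealment exists to protect the last decision to accept or reject a patient. The article promises it up to consent and places a decision on inclusion after consent, so the promise as worded stops short of that decision.

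**Working it through.** The point turns on order, and the plan gives no figure to reproduce. The check sets the sections side by side.

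**1. When is the baseline MAS rated?**
- Table 1 grid: week 0 and week 4. Ticks within the single week 0 column carry no order.
- Table 1 note: this supplies the order, and it puts the first rating after allocation.
- Abstract, Interventions and Outcome Assessments: the first rating is before treatment. That fits a rating on either side of allocation, so it does not overrule the note.
- Week -1 Baseline row: content not stated, so it cannot be taken to contain the scales.

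The only text that orders the two events puts the rating after allocation.

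**2. Is a rating before allocation needed anyway?**
Yes. Entry requires MAS grade I to III, which is 1 to 4 points on the article's 0 to 5 coding. A MAS grade must exist before a patient can be called eligible, but Table 1 schedules none before allocation. Either a screening MAS is taken and is missing from the schedule, or the week 0 rating settles eligibility on this criterion. The article does not say which.

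**3. What would a shifted baseline do?**
Suppose that the mean baseline MAS in one arm is rated *d* points too high and the week 4 ratings are unaffected.
- Difference in change (baseline minus week 4): the bias in favour of that arm is *d*.
- Week 4 adjusted for baseline with slope *b*: the bias is *b* × *d*.
- Week 4 alone: the bias is 0.
- Within-arm comparison of before and after: the bias is *d* in that arm.

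The Statistical Analysis section names *t*-tests or rank-sum tests within and between groups. It does not say whether the between-group comparison uses week 4 values or change. The within-group comparisons use the baseline directly. The document gives no value for *d* or *b*, nor a standard deviation for the MAS.

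**4. Is the final eligibility review protected?**
- Randomization: the assignment is hidden until consent.
- Recruitment: consent, then final review, then inclusion.
- Table 1: the title and layout put screening and consent (week -1) before assignment (week 0).
- Randomization, opening words: those allocated are already eligible.

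The order consent, final review, envelope satisfies all four. The order consent, envelope, final review satisfies the first two and conflicts with the last two. The weight of the text favours the sound order, but the sentence that defines concealment does not secure it.

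**The case against.** The strongest reply has three parts.

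**Eligibility.** A reader might infer that concealment fails and that patients can be dropped at the final review once the arm is known. The documents do not support this. Recruitment says that the review follows consent, not that it follows allocation. Hiding the assignment until consent is a minimum condition and does not mean that the envelope is opened at that moment. The Table 1 title, the week -1 and week 0 layout and the opening of Randomization all put eligibility first. This objection stands, and it reduces the eligibility part to a wording point.

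**Baseline.** Rating after allocation biases nothing unless the rater knows the arm. No treatment has yet been given, patients are said to be blinded, and the Blinding section restricts communication in order to keep the evaluation objective. The MAS entry criterion also implies that an earlier grade exists, against which a drifting baseline might be noticed. This stands in part: no route by which a rater learns the arm is shown. But the experts under the communication rule are not identified as the raters, and no earlier MAS grade is scheduled or designated as the baseline. The safeguard is therefore incomplete.

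**Reach.** A comparison of week 4 MAS alone is untouched by a biased baseline. This also stands, so the concern is limited to analyses that use baseline or change.

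**Conclusion.** The baseline part holds. As written, the reference value of the rater-scored primary outcome, and of the three secondary scales, is taken after allocation, and the article does not state that the raters are blinded. Arm-influenced baseline ratings are possible; nothing shows that they occurred. The missing MAS before allocation is a further inconsistency between the entry criteria and Table 1.

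The eligibility part holds only as a mismatch between the concealment wording in Randomization and the review described in Recruitment, to be reconciled with Table 1.

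No size can be attached. A reader might want a false-positive rate for an assumed rating shift, but the shift, the standard deviation and a change-score analysis would all have to come from outside the document, so such a figure would carry no weight. The conclusion assumes that the Table 1 note means what it says. If baseline was in fact recorded before the envelope was opened, the remedy is only to correct the text.

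**What to change.** For patients still to be enrolled:

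1. Complete the final eligibility review, and record MAS, FMA-UE, CSS and MBI on the CRF, before the envelope is opened.
2. In Table 1, move the baseline ticks for these four rows to before allocation, which also supplies the MAS needed for entry. Reword the note so that the two evaluations fall before allocation and after treatment.
3. In Randomization, state that the envelope stays sealed until consent, final review and baseline recording are all complete.
4. In Blinding, state whether the raters are kept unaware of the arm.

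The cost is a small protocol amendment and a reordering of steps; no extra visit or measurement beyond those already implied is needed. Trial Status says that recruitment began on 1 September 2021 and is ongoing, so the change does not cover patients already enrolled. For them, the report should say when the baseline was rated relative to the opening of the envelope, as far as records allow.

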**Figure 1 F1:**
[figure not shown]
Flowchart of the trial. FA, functional acupuncture; TA, traditional acupuncture; MAS, the Modified Ashworth Scale; FMA-UE, the Fugl-Meyer Assessment for Upper Extremity; CCC, clinical neurological deficit score; MBI, the Modified Barthel Index.

### Randomization

Eligible patients were allocated, in a 1:1 ratio were randomly assigned to the experimental group or the control group, following the randomization principle, which employs block randomization to generate random-number sequence using the SPSS, and an independent statistician who did not participate in the treatment and result evaluation was responsible for processing the results. Meanwhile, we also prepared sealed opaque envelopes with group information strips in these envelopes, which was hidden until the informed consent was obtained.

